#### Cost analysis

All direct medical cost items, expected to be affected by the ECLS therapy will be registered on a patient level, and valued according to the Dutch standard guidelines for economic evaluations [14]. Non-medical costs such as transportation to an ECLS center, informal care and productivity losses/regained productivity (of patient and partner) will be measured by means of a question in the questionnaire. Costs of resource use outside the hospital, such as productivity losses or traveling expenses will be collected using the relevant parts of the iMTA cost questionnaires.

#### Patient outcome analysis

Utility will be measured using the EuroQol (EQ-5D-5 L) at six months and one year. In order to value the EQ-5D profiles, the new Dutch algorithm will be used [15]. The use of the EQ-5D as a generic measure in economic evaluations facilitates the comparability of (cost effectiveness) results across different studies and interventions.

#### Budget impact analysis (BIA)

Budget impact analysis will be performed from a health care perspective, and in addition from health insurance perspective. The base care scenario will focus on 1 year impact on a national level. Scenario analysis will adopt a 5 to 10 year horizon (life time).

Cost-analysis: A BIA will be conducted to inform decision-makers about the financial consequences of the adoption and diffusion of the use of ECLS in the Dutch healthcare system. The BIA will use a deterministic model. The model input parameters will mainly be based on results of the recently conducted cost study (hospital perspective), the current clinical and cost-effectiveness study, and available literature. The analyses will be conducted from various perspectives, including a direct medical perspective, a budgetary care perspective and a health insurers perspective. For the analysis from a direct medical perspective, only cost within the healthcare sector will be taken into account. Unit prices will be based on Dutch standard prices. For the other perspectives, national tariffs will be applied and the scope of included costs will be limited to those relevant for the perspective concerned. The precision of costs will be in accordance with the described perspectives (€M).

Given the fact that for the populations under study, the standard care consists of ‘no ECLS’, the model will only take changes in the availability and adoption of the use of ECLS into account by calculating the financial consequences of the following scenarios:Situation in which all patients that are in principal suitable to use receive ECLS treatment, will receive standard care in the hospital, according to the current practice, which means no ECLSSituation in which all suitable patients receive ECLS according to the current study protocolSituation in which ECLS utilization will gradually be implemented in new hospitals.Situation in which ECLS is considered suitable and available for varying percentages of the targeted populationSituation in which the indication for ECLS will gradually be broadened.

For each of the presented scenarios, a time horizon up to 5–10 years will be applied. Alternative time horizons will be addressed in sensitivity analyses. Costs will be calculated based on changes in resource use, valued against the price level relevant from the various perspectives. Discounting of future costs will not be applied in the BIA. The model will allow additional analyses for subgroups of patients. These analyses mainly include the shift in the subgroups of patients based on indication and severity. Budget information for relevant subgroups will be made available for decision makers. The planned sensitivity analysis will address the main input parameters and assumptions of the model, and financial consequences of variations in model parameters will be calculated for each of the applied perspectives [16].

## Discussion

The study uses a prospective observational design and not of a randomized controlled trial. A randomized controlled trial in ECLS would be very challenging for both the logistic and ethical reasons. We expect in the current time that the initiation of a randomized controlled trial would lead to bias and therefore impairing the external validity of the results. Our observational design with the use of predicted mortality of individual patients at the moment of initiating of ECLS as an internal comparison resembles the methods of a randomized controlled trial the most. In contrast to a randomized controlled trial our design prevents bias on the basis of indication and selection because all consecutive patients will be included. This guarantees the inclusion of a real world patient population that is clinical relevant.

ECLS is currently offered in many centers worldwide, but application per population range enormously even within countries. It is estimated that in some regions the amount of eligible patients is 10-fold the current number. Although assumed to be beneficial in terms of life saving application may be hampered by the apparent high costs and that ECLS is not covered by the health insurance in some countries. In summary, we expect that ECLS treatment is cost-effectiveness, in this case defined as having an additional benefit worth the additional cost. When cost-effectiveness is made plausible, a gradual increase in ECLS therapy is expected from which many patients will benefit.

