## Background

Extracorporeal life support (ECLS) by means of extracorporeal membrane oxygenation (ECMO) utilization can support the heart and lung for an extended period of time, up to months, an is deployed in the Intensive Care Unit (ICU). The indication for ECLS is acute, potentially reversible cardiac or respiratory failure, when conventional therapy has been inadequate [1]. In addition, ECLS can also be used in patients with terminal respiratory or cardiac failure as a bridge to transplant, and to support cardiopulmonary resuscitation; extracorporeal cardiopulmonary resuscitation.

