A direct comparison between usual care and ECLS, e.g. by means of a randomized trial, is very complex since standard treatment (no ECLS) will result in death in a vast majority of cases. However, several ICU scoring systems exist that predict hospital mortality of individual patients. Depending on the indication, i.e. underlying disease, RESP score, SAVE-score, APACHE-4, SAPS-III or SOFA score are the most reliable for that purpose [5–9].

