### Inclusion criteria

All adult patients who receive ECLS will be included. With our consortium we cover nearly all ECLS treatments in The Netherlands. In general, according to the ELSO guidelines, ECLS can be considered in acute severe heart and/or lung failure with high mortality risk despite optimal conventional therapy. ECLS is indicated in most circumstances at 80% mortality risk. Severity of illness and mortality risk is measured as precisely as possible using measurements for the appropriate age group and organ failure.

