### Ethics

The need for ethical approval was waived by the institutional medical ethics board of the University Medical Center of Groningen (protocol number METc 2017/196), and written informed consent will be obtained from all patients or legal representatives.

The predicted mortality for every patient at the initiation of ECLS is used and compared with the actual mortality at one year of each patient. That means that every patient acts as his own control. Depending on the indication or the underlying disease, the APACHE-4, SOFA score, RESP score, or SAVE score will be used to estimate mortality. Although the used models predict hospital mortality instead of one year mortality, the vast majority of mortality is during hospital admission, so the used mortality prediction is expected to be valid for one year survival analyses as well [10, 11].

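### The Discussion says the design prevents indication and selection bias, but enrolling every ECLS-treated patient cannot do that when the control is a score-predicted mortality

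*Protocol article*

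**What the plan says.** The cohort is defined by treatment: "All adult patients who receive ECLS will be included" (Inclusion criteria). The Background gives the basis for treating: "The indication for ECLS is acute, potentially reversible cardiac or respiratory failure, when conventional therapy has been inadequate". It adds bridging to transplant and support of resuscitation as further uses.

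The comparator is a prediction. The Background notes that "several ICU scoring systems exist that predict hospital mortality of individual patients". The paragraph on predicted mortality, printed under Ethics, says that, depending on indication or underlying disease, "the APACHE-4, SOFA score, RESP score, or SAVE score will be used to estimate mortality". It continues: "The predicted mortality for every patient at the initiation of ECLS is used and compared with the actual mortality at one year of each patient". From this it concludes: "That means that every patient acts as his own control".

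The Statistics section uses the same predicted mortality as the comparator for QALYs. The cost-effectiveness section then compares ECLS with usual care in cost per QALY and acceptability curves.

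The Discussion presents the prediction as an internal comparison that comes closest to a randomised trial. It then says, as an advantage over such a trial, that "our design prevents bias on the basis of indication and selection because all consecutive patients will be included".

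**The concern.** Bias by indication arises when clinicians decide who is treated. Enrolling everyone who was treated keeps that decision in the cohort. Randomisation is what removes it, so the contrast with a randomised trial is the wrong way round.

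Calling each patient his own control does not repair this. The control value is a model output, not an outcome observed in that patient without ECLS. If clinicians use information beyond the score, the selected patients' true untreated mortality can differ from the prediction, and that difference is credited to or taken from ECLS. The problem would remain with a perfect one-year score, so it is separate from the only benchmark weakness the article discusses, which is hospital versus one-year mortality.

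At stake are the survival difference, QALY gain, cost per QALY and acceptability curve, all of which would be reported as free of a bias that the design cannot exclude.

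**Working it through.** **1. What the design fixes and what it leaves open.** Consecutive enrolment controls which treated patients enter. It says nothing about eligible patients who were not treated, and the article describes no such group. Two selection pressures can be read from the document:
- Choosing failure judged potentially reversible could make true untreated mortality lower than predicted.
- Choosing patients in whom conventional therapy has failed, or "ECLS can be considered in acute severe heart and/or lung failure with high mortality risk despite optimal conventional therapy", could make it higher.

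Nothing in the study measures which dominates.

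**2. How the plan treats the prediction.** Inputs from Sample size calculation: usual-care mortality 80%, ECLS mortality 38%, 25 patients for survival with RR 0.48 (0.28–0.82), and 200 analysed with RR 0.82 (0.75–0.90). The article does not state alpha or power; I assume two-sided 5% and 80%.
- Two proportions, 80% v 38%, continuity-corrected: 25 per arm.
- SE(log RR) = √[(1−p₀)/(n·p₀) + (1−p₁)/(n·p₁)]. With 25 v 25: RR 0.475 (0.277–0.813), close to the stated interval.
- With 200 v 200 at 90% v 74% poor outcome (69% plus the plan's 5-point allowance): RR 0.822 (0.748–0.903), matching the stated interval.

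The intervals are reproduced when the prediction is treated as an equal-sized control arm, so the planning takes it as these patients' true untreated risk.

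**3. If ECLS did nothing and the prediction were too high.** The article does not state the test, so I show two, with n = 200 and an 80% benchmark.
- One-sample exact binomial, lower tail at most 2.5%: benefit is declared at 148 or fewer deaths, P(X ≤ 148 | 0.80) = 2.4%.
- Two-sample comparison, 200 v 200, two-sided 5%.

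| Assumed true usual-care mortality | Two-sample | One-sample |
|---|---|---|
| 78% | 7% | 10% |
| 75% | 22% | 40% |
| 70% | 64% | 91% |

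These mortalities are assumptions; the documents give no figure for selected patients. In the other direction the risk shrinks: at 82%, P(X ≤ 148) = 0.3%.

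**4. If ECLS performs as expected.** At 38% mortality, 76 of 200 die, and the exact upper 95% limit is 45%. In the one-sample comparison, significance is lost only when the benchmark falls to about 45%, a logit shift of ln(0.45/0.55) − ln(0.80/0.20) ≈ −1.6. In the two-sample version the figure is about 48%, a shift of about −1.5.

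**5. Effect size at 38% ECLS mortality.** QALY gain = (m − 0.38) × 0.83, where m is usual-care mortality and 0.83 is the expected quality of life in Statistics. At m = 80% this gives 0.42 × 0.83 = 0.349. The article states 0.36; the small gap does not affect this point. For cost per QALY I hold the article's €172,200 additional one-year cost fixed. That is a simplification: the article says costs should exceed it, and usual-care costs would themselves change with survival.

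| m | QALY gain | One-year € per QALY |
|---|---|---|
| 89.4% (logit +0.75) | 0.427 | about 403,000 |
| 80% | 0.349 | about 494,000 |
| 75% | 0.307 | about 561,000 |
| 70% | 0.266 | about 648,000 |
| 65.4% (logit −0.75) | 0.227 | about 757,000 |

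**The case against.** The sentence can be read as a statement about generalisability. The text before it mentions external validity, and the sentence after it speaks of a real-world population. On that reading consecutive enrolment does help, and this part stands. But the sentence names indication bias, sets itself against a randomised trial, and follows the claim that the prediction resembles one. A reader will take it as a claim about the validity of the comparison, and as such it is wrong.

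The primary outcome, EQ-5D-5L at 12 months, and the primary economic aim, societal costs, do not use the benchmark. That stands and limits the reach of the point.

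Scores are chosen by indication or underlying disease, and the document does not say in which populations they were built. So it cannot be asserted that they are miscalibrated here, only that their calibration in ECLS-selected patients is not shown.

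Scenario analyses are already planned, and an article may leave their content to a fuller document. That is fair, but unspecified scenarios do not correct an affirmative statement that the bias is absent.

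A reader might infer that selection favours ECLS, or that the expected survival benefit could be an artefact. The documents do not support either. Conventional-therapy failure pushes the other way, and a false declaration needs observed mortality near 74%, whereas the plan expects 38%.

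**Conclusion.** The Discussion attributes to the design a property it does not have, and the claim should be corrected. The comparison with usual care rests on a score prediction whose calibration in ECLS-selected patients is unknown, in either direction. If results come out as planned, the survival conclusion is robust: the benchmark would have to fall from 80% to about 45–48%. What changes realistically is size. Over assumed benchmarks of 75% to 65.4%, the QALY gain falls from 0.349 to between 0.307 and 0.227, and upward shifts raise it. The false-declaration rates (7–10%, 22–40% and 64–91%) apply only if ECLS has no effect, and depend on the assumed true mortality and on a test the article does not state. They illustrate sensitivity and do not predict this study's result.

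**What to change.** In the Discussion, delete the claim that the design prevents bias by indication and selection. State instead that patients selected for ECLS are compared with a score-based prediction whose calibration in them is unknown, and that consecutive enrolment supports generalisability.

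In the predicted-mortality paragraph under Ethics, and in Statistics and Cost effectiveness analysis, name one of the planned scenario analyses: shift every patient's predicted mortality down and up on the logit scale. At each shift, repeat the survival difference, QALY gain, cost per QALY and acceptability curve. Report the shift at which the benefit or the cost-effectiveness conclusion changes. No pass/fail rule at a fixed shift is proposed, because the documents give no basis for choosing one.

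The cost is a wording change and existing analyses rerun over a grid, with no new data. The downside is that the benefit claim becomes more conditional.

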### Trial status

The trial is registered at https://clinicaltrials.gov/ (NCT02837419), registration date July 19, 2016.

The trial is registered at the Dutch Trial Register at July 27 2017 http://www.trialregister.nl/trialreg/admin/rctview.asp?TC=6599

Recruitment will start at December 2017, recruiting during 18–24 months, with a 1 year follow up.

## Abbreviations

ARDS: Adult respiratory distress syndrome
ECLS: Extracorporeal life support
ECMO: Extracorporeal membrane oxygenation
ICU: Intensive Care Unit
QALY: Quality adjusted life year
QoL: Quality of life
VAS: Visual analogue scale
